## 2. Methods

### 2.1. Study design

Randomized crossover trials, clinical experiments in which participants are assigned randomly to a sequence of treatments and each participant serves as one’s own control in estimating treatment effect (Senn, 2002; Piantadosi, 2005), will be used in the present study. Participants will be assigned randomly to either rhythm training followed by cognitive training or cognitive training followed by rhythm training (Figure 1). For both groups, pre- and post-training evaluations will be administered immediately before training and after the 4th week of training. Participants will have a 4-week washout phase between trainings to minimize a possible carryover effect (Senn, 2002; Piantadosi, 2005). Pre- and post-training evaluations will include diagnosis questionnaires, cognitive evaluation tools, and resting EEG measurement.

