### 2.3. Recruitment

Participants who have met the eligibility criteria will be enrolled in the study after they provide informed consent. Participants and their parents will receive oral and written information detailing the purpose of the study. All experimental protocols will be approved by the Institutional Review Board of Hanyang University Medical Center. Approximately 40 children with ADHD will be recruited through Hanyang Medical Center outpatient clinics or online recruitment posts. The criteria to be included in the examination are as follows: (1) 8 ≤ age ≤ 15; (2) satisfied the criteria of ADHD based on *Diagnostic and Statistical Manual of Mental Disorders 4th edition* (DSM- IV) and diagnosed with ADHD based on the *Korean version of Kiddie-Schedule for Affective Disorders and Schizophrenia-Present and Lifetime* (K-SADS-PL) in a semi-structured clinical interview conducted by a single board-certified psychiatrist; (3) intelligence quotient (IQ) score above 70; (4) have not received medication for ADHD treatment in the past or have received medication in the past but for less than 1 year and not within 4 weeks of the study. The exclusion criteria are as follows: participants with (a) congenital hereditary problems; (b) acquired brain injury such as cerebral palsy; (c) spasmodic disorder, other neurological disorders, or untreated dysesthesia (sensory disturbance); (d) diagnostic history or current state of schizophrenia and childhood psychosis; (e) intellectual disability; and (f) comorbid condition with obsessive-compulsive disorder, depressive disorder, or bipolar disorder. Comorbid conditions, such as anxiety or enuresis, will be allowed except for the symptoms in exclusion criteria. In addition, participants could apply the medication targeting other types of coexist pathologies, not with the symptoms which meet the exclusion criteria.

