### 2.7. Statistical analysis

All statistical analyses will be conducted using SPSS statistical software (version 24.0, SPSS, Inc., Chicago, IL, USA). The study will undertake a comparative analysis of two intervention sequences and investigate the existence of carry-over effects. This will involve conducting *t*-tests on the change of each sequence for all crossover endpoints (Wellek and Blettner, 2012; Jones and Kenward, 2014). For variables that do not show significant carry-over effects, we will compare the changes during specific interventions in both sequences. For variables that show significant carry-over effects, we will compare the changes in specific interventions during the first period. To confirm the normal distribution of the data, we will analyze the skewness and kurtosis and perform the Shapiro-Wilk and Kolmogorov–Smirnov tests. Firstly, the differences between rhythmic sequences will be compared using repeated measures ANOVA (RMANOVA) and the Bonferroni correction for pairwise comparisons. If the data do not satisfy a normal distribution, Friedman’s test one-way analysis of variance (ANOVA) will be performed. Secondly, Pearson’s correlation test will be used to calculate the correlations between RAT performance and behavioral outcome measures. Thirdly, differences of EEG band activities between the types of rhythmic sequences and the tasks will be compared using RMANOVA with Bonferroni correction. Lastly, comparisons between interventions will be performed using a two-tailed *t*-test or Mann–Whitney U test depending on normality.

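### For endpoints without carry-over, the intervention comparison reads as an unpaired test on two changes from the same children, with no period adjustment

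*Protocol article*

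**What the plan says.** Section 2.1 of the protocol article adopts a two-sequence crossover in which "each participant serves as one’s own control in estimating treatment effect". Children receive rhythm training (RAT) then cognitive training, or the reverse, with a 4-week washout between. Section 2.3 plans for about 40 children. The test battery is given before and after each training period.

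Section 2.7 first tests for carry-over and then takes one of two branches:
- Carry-over found: only the first-period changes are compared.
- Carry-over not found: "we will compare the changes during specific interventions in both sequences".

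The test for the intervention comparison is given at the end of the section: "Lastly, comparisons between interventions will be performed using a two-tailed *t*-test or Mann–Whitney U test depending on normality". It is not said whether the t-test is paired, or on which quantity it is run. No paired test, within-child difference, period term or mixed model is named for this comparison. The same section does name methods for dependent data elsewhere: repeated-measures ANOVA and Friedman's test for the rhythm types, and repeated-measures ANOVA for EEG.

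**The concern.** In the no-carry-over branch every child supplies one change under each intervention. Mann-Whitney U is an independent-samples test, and the t-test offered as its normal-data counterpart is most naturally the two-sample one. Applied to changes sorted by intervention, these tests use a standard error that ignores the within-child correlation. They are conservative and lose power if the two changes correlate positively, and reject too often if they correlate negatively.

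Period is the second issue. The same digit-span, Stroop, colour-trails and continuous-performance tests are taken four times in about 12 weeks (4 training + 4 washout + 4 training), so practice gains may differ between the periods. Without adjustment, such a difference enters the error term. It also enters the estimate if the sequences are of unequal size.

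This comparison serves the fourth hypothesis in the Introduction, the one that depends on the randomisation.

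**Working it through.** The article gives no power calculation, alpha, SD, correlation or period effect for this comparison, so there is no planned figure to reproduce. What can be computed is how the test behaves as written.

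**Inputs.** From the document: two sequences, about 40 children, two-sided test. Assumed: 20 children per sequence, SD of each change = 1, alpha 0.05, true difference 0.5 SD where power is given, within-child correlation of the two changes rho from -0.25 to 0.5, and period effect 0 to 1 SD.

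**1. Pairing, no period effect.** The unpaired test assumes a variance of 2/40 for the difference in means. The true variance is 2(1 - rho)/40. Its actual type I error is therefore about 2[1 - Φ(1.96/√(1 - rho))]:
- rho = -0.25: 1.96/√1.25 = 1.753, giving 8.0%
- rho = 0: 5.0%
- rho = 0.25: 1.96/√0.75 = 2.263, giving 2.4%
- rho = 0.5: 1.96/√0.5 = 2.772, giving 0.6%

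Monte Carlo runs agree: 7.6% to 8.0%, 4.8% to 5.0%, 2.5% to 2.7%, and 0.6%. Mann-Whitney U on the same pooled changes behaves almost identically.

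**2. Power for 0.5 SD, no period effect.** The comparator is a two-sample t-test between sequence groups on each child's period-1 minus period-2 difference. The sequence groups then differ by 2 × 0.5 = 1.0, and the SD of the difference is √(2(1 - rho)).

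| rho | Unpaired, pooled by intervention | Between-sequence test on period differences |
|---|---|---|
| -0.25 | 59% (type I error about 8%) | 49% |
| 0 | 59% to 60% | 58% to 59% |
| 0.25 | 61% | 71% |
| 0.5 | 63% | 87% |

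The higher figure for the unpaired test at -0.25 is bought with its inflated type I error.

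**3. Which rho is plausible?** The outcome is change from each period's own baseline, so stable differences between children cancel. If all four visits are equally correlated, the covariance of the two changes is r - r - r + r = 0. If correlation decays as equally spaced AR(1), the correlation of the changes is -r(1 - r)/2: -0.125 at r = 0.5 and -0.045 at r = 0.9. At -0.125 the formula in step 1 gives 6.5%. A positive rho would arise if some children gain more than others from any training. The documents do not settle this.

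**4. Period effect, balanced sequences.** Half of each pooled group carries the period shift p, which adds about p²/4 to the variance the test estimates. For p = 1 that is 1.25 instead of 1. The estimate stays unbiased, but at rho = 0 type I error falls to about 2.8% and power to about 50%, against 58% for the between-sequence test. At rho = 0.5 power is 51% against 87%.

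**5. Period effect, unequal sequences.** The pooled contrast is biased by p(n1 - n2)/(n1 + n2). With 20 and 14 completers and p = 0.5, this is 0.5 × 6/34 = 0.088 SD.

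**6. Would a plain paired t-test do?** It repairs the pairing but not the period. At rho = 0.5 its type I error is 5.1%, 2.9% and 0.5% for period effects of 0, 0.5 and 1 SD. The between-sequence test stays at 4.7% to 5.5% in every setting tried.

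**The case against.** The strongest reply is that the words independent-samples and pooled are not in the article. A two-sample t-test or Mann-Whitney U between sequence groups, run on within-child period differences, is a valid crossover analysis and uses exactly the two tests named. Section 2.7 also opens by comparing the two sequences and cites crossover methodology. This reading stays open, and it lowers confidence that there is an error of method and not only of wording. It does not remove the point, because the text says the changes during each intervention are compared and never mentions a within-child difference.

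Further points that stand:
- In the first-period-only branch the groups are independent, so the named tests are right.
- At rho near zero, which is plausible for change scores, the loss nearly vanishes.
- A period effect biases nothing while the sequences are balanced. The 20/14 split and the 0.5 SD shift are illustrations, not figures from the plan.

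Another reply is that an article leaves such detail to a fuller analysis plan. That would cover silence on a period term alone. Here the article names the data and the tests, and as written they do not fit together.

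A reader might infer that the trial's p-values are certainly wrong, or that the plan knowingly counts 40 children as 80 independent observations. The document supports neither: the first depends on an unknown correlation and period effect, and the second is an inference from the choice of tests.

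**Conclusion.** The point holds for endpoints analysed over both periods. On its plain reading, section 2.7 does not use the property for which section 2.1 chose the crossover, and its error rate is nominal only when the two changes are uncorrelated and the periods do not differ. How far it departs, and in which direction, rests on assumed values: from about 8% to 0.6% type I error over correlations of -0.25 to 0.5, with a power loss of up to 24 percentage points (87% - 63%) at 0.5 and almost none at 0. The practical effect may be modest. This should be fixed, and confidence is moderate, because a valid analysis may be what was meant.

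**What to change.** In section 2.7, state the quantity tested. For endpoints analysed over both periods, compare each child's period-1 minus period-2 difference in change between the two sequence groups by a two-sample t-test, or by Mann-Whitney U on those differences. Half the difference between the group means estimates the intervention effect, free of period. Equivalently, fit a mixed model with intervention, period and sequence as fixed effects and child as a random effect. State separately that the unpaired test on the changes themselves is kept for the first-period-only branch. The cost is one paragraph. No new data are needed, and the first option uses only tests that the section already names.

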## 3. Discussion

The current study aims to develop RAT as a tool for assessing and training the time-related abilities of children with ADHD using a wide range of auditory stimuli organized in various types of rhythmic sequences. Additionally, the study will validate rhythm-based attention training for children with ADHD and its correlations with the behavioral diagnostic questionnaire and scores of cognitive evaluation tools for ADHD. In addition, they study will examine the efficacy of the training in comparison with general cognitive training. The use of EEG will aid in uncovering the nature of auditory rhythm processing in ADHD and in revealing the therapeutic mechanism of auditory rhythm at various levels of complexity. The present findings will contribute to the potential of rhythm-based training as a supplementary or alternative method for behavioral symptoms and cognitive functions of ADHD. The multifaceted data collected will provide valuable insights into the development of a computerized rhythm-based cognitive training program for ADHD and will enable tailored training agendas based on individual developmental stages and prognoses.

The RAT might capture a more comprehensive picture of an individual’s timing ability and potentially lead to more personalized and effective interventions in various clinical and educational contexts. Firstly, the present study could potentially establish the RAT as a new music-based intervention for managing timing-related problems in ADHD. The specific study protocol enables music therapists to measure and quantify musical responses and clearly indicates how changes in musical responses are related to and can lead to symptom-related changes and cognitive enhancement. The behavioral data collected in this study could enable more tailored music-based interventions and, thus, improve the effectiveness of interventions and patient outcomes. Also, by using EEG measurements, the study may provide novel insights into the underlying neural mechanisms of how auditory rhythm can impact cognitive functioning for children with ADHD. This would expand the therapeutic arsenal available to clinicians, offering a non-pharmaceutical intervention that could be used either independently or in conjunction with other treatments. Given the mutual enhancement of WM and cognitive flexibility through rhythm and verbal tasks, an inclusive strategy could improve a deeper understanding between rhythm-related timing ability and cognitive functions.

## Ethics statement

The studies involving human participants were reviewed and approved by the Institutional Review Board of Hanyang University Medical Center (Approval No. 2020-02-025). Written informed consent to participate in this study was provided by the participants’ legal guardian/next of kin.
